#### Description Analysis

In the bio section, people generally write about themselves or any famous quote they like or that resembles them. Sometimes, it can be one or multiple lines or even just a word. In the details section, they can add current and previous workplaces, institutions, relationship status, hobbies, and cities they previously lived in and currently live in. People with mental health issues have a tendency not to share their information with everyone. They have a close group of people with whom they feel comfortable sharing information [57]. It is often seen that the bio and details sections of these people remain almost empty or filled with very little information.

#### Content Analysis

Studies have consistently shown that people are willing to share their depression and medical conditions on various social networking sites [83]. Related studies have investigated language and emotional patterns and successfully assessed new mothers’ postpartum behavioral changes from prenatal assessments [84]. These findings highlight the potential of SM as an important indicator in assessing the occurrence of current or future depression.

In our study, we aim to introduce measures that evaluate and characterize users’ linguistic styles in posts, comments, and search history, irrespective of whether they are anonymous. An important observation is that users who are depressed post personal content in various groups or pages anonymously. This behavior seems driven by the need for a safe, nonjudgmental space to express emotions and seek support. In addition, depression-related content, such as quotes, internet memes, and music, is prevalent among users. Examples include posts including “sad songs” and “mental illness quotes,” along with expressions of feelings of despair and overwhelm, such as “I am so lonely” and “Everything seems too overwhelming and pointless.” Understanding such patterns of anonymously shared data on SM platforms can provide valuable insights into predicting the mental health challenges people face. Moreover, analyzing such content and the frequency of posting may be instrumental in identifying depression and the potential areas for targeted interventions and support.

This study also highlighted the untapped opportunity in understanding users’ search activity, which holds promising potential for enhancing clinical and public health efforts in suicide risk assessment and prevention. Participants’ search themes encompass suicide, help-seeking, mood and anxiety symptoms, and trauma and negative life events [85]. Often, users facing trauma or negative life events search for support resources, coping strategies, and information on seeking professional help. This includes asking questions about outpatient resources, health clinics, and other medically relevant topics, analyzing which helps gain a comprehensive understanding of users’ mental health concerns. Further, to enhance the robustness of the predictive model, in this study, we focus on additional insights into users' engagement with relevant resources and communities over Facebook. By integrating a comprehensive list of the user’s group memberships, liked pages, and notification messages, we provide a holistic approach to understanding users’ mental health, allowing us to develop effective strategies while assessing suicide risk at an early stage.

In this research paper, we will preprocess the text data to ensure their suitability for subsequent model building. Given the unstructured nature of SM data, we will apply customized preprocessing and cleaning techniques. These techniques include removing accented characters; expanding contractions; converting to lowercase; eliminating URLs, symbols, digits, and special characters; fixing word lengthening; applying spelling correction; removing stop words; and performing lemmatization. These steps will aim to standardize the text, reduce dimensionality, improve data quality, and ensure consistent representation in our models. By implementing these preprocessing steps, we will be able to successfully clean and prepare the text data, making them suitable for subsequent analysis and model training [74].

During the data cleaning phase, we will take additional steps to refine the preprocessed text data. These steps will involve removing irrelevant words, empty rows, and outlier rows with high word counts. By eliminating irrelevant words, we will focus on more meaningful features for analysis. The empty rows, which will not contain any useful information, will be dropped to ensure data integrity. At the same time, the outlier rows with high word counts, deviating significantly from the majority, will be removed to optimize model training efficiency. These measures will improve the data set’s quality and relevance, preparing it for further analysis and model training.

Further, we will use a vectorizer called Tf-idf Vectorizer to transform our textual data into numerical features suitable for ML algorithms. That vectorizer will can be configured with specific parameters: min_df=50 and max_features=5000. The min_df parameter specifies that a word must appear in at least 50 documents (posts, in our case) to be included in the feature representation. This will help filter out infrequently occurring words that may not contribute significantly to the overall understanding of the data. The max_features parameter sets an upper limit on the number of features (words) to be considered. In our case, we will set it to 5000, indicating that only the top 5000 most relevant features (based on their frequency) will be selected for further analysis. This approach will enable us to represent the text data numerically, capturing the importance of different words while reducing the dimensionality of the feature space.

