### Text and Behavior Analysis

#### Overview

We are planning to use NLP techniques to analyze the linguistic patterns and sentiments in user-generated content. We will also identify language indicative of depressive symptoms, negative emotions, and expressions of hopelessness. We will use LIWC and Affective Norms for English Words lexicon categorization for more accurate results in the text analysis [79]. In addition, we will use topic modeling and keyword extraction to identify prevalent themes within the text. These insights are essential for understanding trends, preferences, or concerns within the data set.

Behavior has 2 divisions: post-centric behavior and user-centric behavior. Post-centric behaviors include post time, number of posts, posting frequency, friends, followers, likes, replies, comments, and emoji counts. User-centric behaviors include positive affect, negative affect, activation, dominance, linguistic style, depression lexicon, and antidepressant use. Linguistic style specifically shows the total word count, first-person and third-person pronouns, functional words, assent, negation, etc.

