For “negative” emotions from posts for “diurnal activity,” we will be applying the text2emotion Python function to extract the emotional words used on the posts. However, the text2emotion library shows 5 different emotions, namely happy, sad, angry, surprise, and fear. However, here, we will be dealing with the negative feelings from Facebook posts.

First, our main purpose is to clean the data to make them appropriate for analyzing emotions. For the data cleaning process, we need to follow several steps. For instance, we need to remove the unwanted texts or words from the posts (ie, the words that have low frequency based on term frequency–inverse document frequency), apply various tools of the Natural Language Toolkit for sentiment analysis, and extract the better-preprocessed posts from the previous preprocessed posts. Second, we need to figure out the emotional words from the preprocessed texts and then use them for further visualization of the emotions. Finally, we need to observe the scores of the emotions. The higher the score from 1 of the 5 categories, the more the emotion will belong to that group.

After that, we intend to observe the emojis from the posts to investigate what type of nonverbal attributes a person who is depressed has both during the daytime and nighttime while writing posts on SM. This will help us figure out which emojis a person who is depressed uses repeatedly during the night. Several studies were conducted on emojis [89-92], indicating how they coincide with the linguistic style of a person. For instance, the emojis that are inclined with the negative words from LIWC are “anger,” “money,” “ingest,” “family,” “home,” and “death” [89].

As mentioned earlier, we will be focusing on the sentiments in the posts and the frequently used emojis by an individual during nighttime. Moreover, we will be considering how the emotions in a person’s post and the number of emojis used on a post are correlated with diurnal activity. For that, we will be using the formula for MI, as it consists of both joint probability and marginal probability. “Joint probability” will help investigate the relationship between the emotions in the posts and the number of emojis used, applying a condition, that is, if we work on the sentiments in the posts, then the number of emojis will be kept constant, and vice versa. In contrast, “marginal probability” will help us extract 1 feature at a time (ie, the features will be independent of one another).

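### The listed text cleaning would delete emojis, and probably pronouns, function words and negations, that the plan also measures; no raw-text stream is kept

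*Protocol article*

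**What the plan says.** **Cleaning.** In Content Analysis the protocol article says "we will apply customized preprocessing and cleaning techniques". The list opens with "removing accented characters; expanding contractions; converting to lowercase" and continues with "eliminating URLs, symbols, digits, and special characters; fixing word lengthening; applying spelling correction; removing stop words; and performing lemmatization". The stated result is text cleaned and prepared, "making them suitable for subsequent analysis and model training". No stop list is named.

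**Row removal.** The same section then refines the already preprocessed text. It drops empty rows as uninformative, and "the outlier rows with high word counts, deviating significantly from the majority, will be removed to optimize model training efficiency". No cutoff is given. The TF-IDF step follows.

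**Planned features.** The Overview under Text and Behavior Analysis lists emoji counts among the post-centric behaviors. Of the user-centric ones it says: "Linguistic style specifically shows the total word count, first-person and third-person pronouns, functional words, assent, negation, etc".

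**Emotion and emoji analysis.** Diurnal Activity removes words of low TF-IDF frequency, applies sentiment tools, and plans to "extract the better-preprocessed posts from the previous preprocessed posts". Emotional words are then taken from the preprocessed text and scored. The next step reads: "After that, we intend to observe the emojis from the posts". Formula (4) is the mutual information between Po (post negative or not) and E (emoji used or not).

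**The concern.** Cleaning of this kind suits a bag-of-words model. It does not suit features that consist of the very items being removed. Emojis are symbols. Pronouns, function words and, on many lists, negations are the usual content of a stop list. If one cleaned text feeds every analysis, the emoji and linguistic-style predictors lose most or all of their variation, and no later modelling step can recover it.

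Three further consequences follow from the text.

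- Emotion scoring runs on cleaned text after a low-frequency word filter. A rare but strongly emotional word can be lost, and so can the negation that reverses a common one.
- The Results section says that posts without an emoji are classified on their negative-word score. If emojis have been stripped, every post falls into that route.
- A post that consists only of emojis becomes empty and is discarded, and long posts go for reasons of training efficiency. In a study of suicidal ideation, neither kind of post can be assumed uninformative.

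**Working it through.** The protocol gives no figure on this point, so there is nothing to reproduce. The check has four parts.

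**1. Which text feeds which feature**

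| Feature | Source text according to the protocol | Order |
|---|---|---|
| Emotion scores | Preprocessed text, after the low-frequency filter | Explicit |
| Removal of empty and long rows | Preprocessed text | Explicit |
| Emoji features and E | The posts; raw or cleaned not stated | Implied by sequence |
| Pronouns, function words, negation | Not stated | Implied by the general purpose given for cleaning |

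No section keeps a raw copy or exempts any of these items.

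**2. Are the items covered by the deletion steps?**

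- Six common emojis were tested. All are in Unicode category So (symbol), so removing symbols deletes them whatever stop list is used.
- One widely used default English stop list (scikit-learn, 318 words) contains every first- and third-person pronoun tested, every function word tested, and the negations *no, not, never, nor, none, nothing* and *cannot*. It contains none of the assent words tested (*yes, ok, okay, agree*).
- The protocol does not say that it will use this list. It serves only as an example.

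**3. The steps applied to six short posts**

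Two of the posts are adapted from expressions in Content Analysis and four are invented. Contractions were expanded and text lowercased, symbols were removed, and a short assumed stop list was applied, once with and once without negations.

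| Count over six posts | Raw | Cleaned, negations on list | Cleaned, negations kept |
|---|---|---|---|
| Tokens | 35 (31 words + 4 emojis) | 12 | 15 |
| Pronouns | 6 | 0 | 0 |
| Function words | 16 | 0 | 0 |
| Negations | 3 | 0 | 3 |
| Emojis | 4 | 0 | 0 |

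The function-word zero holds by construction, because the function words counted are those on the assumed list. The contrast between the last two columns shows that the loss of negations depends on the list and the loss of emojis does not.

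With negations on the list, *I am not happy* becomes *happy* and *I'm not sad today* becomes *sad today*. The two shifts go in opposite directions. An invented post, *I cannot go on*, has every word on the 318-word list, so it would be emptied and then dropped.

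**4. Mutual information once emojis are stripped**

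MI = Σ P(po,e) · ln[ P(po,e) / (P(po)·P(e)) ]. The two tables below are assumed, with 1000 posts each. The full 2×2 table is used in order to isolate the effect of cleaning. The section's separate statement about leaving out some combinations of Po and E is set aside here.

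- Weak association, cells (Po=0: 350, 350; Po=1: 120, 180): 0.02166 − 0.02039 − 0.01935 + 0.02233 ≈ 0.0042.
- Strong association, cells (Po=0: 500, 200; Po=1: 90, 210): 0.09558 − 0.07223 − 0.06087 + 0.11233 ≈ 0.0748.
- Emojis stripped, so E = 0 in every post: P(po, E=0) = P(po) and P(E=0) = 1. Each logarithm is ln 1 = 0, so MI = 0 for any data.

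**The case against.** **Order.** Content Analysis first gives the purpose of cleaning as model building and leads straight into TF-IDF, so it may be meant for that stream alone. Emotional words are taken from preprocessed text but emojis from the posts, and that difference in wording may be deliberate. This stands in part. A reader might infer that the plan definitely counts emojis and pronouns after deleting them, and the document does not say so. But the cleaning is also said to serve later analysis, and nothing reserves a raw stream.

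**Stop list.** It is unnamed and the cleaning is called customized, so negations may be kept. This stands: zero negation counts are conditional. It does not help emojis, and pronouns and function words are ordinary stop-list content.

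**Sentiment.** A reader might infer that emotion scores would be biased toward positive. That is not supported, because stripped negation moves scores both ways and the net sign is unknown. The protocol also does not say that its emotion tool would otherwise use negation.

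**Unique features.** A reader might infer that the plan could not test the features it calls unique. Of those named in the Introduction and in Comparison With Previous Work (games, advertisements, anonymous posts, emojis, stickers, bio sections), only emojis are shown to be affected.

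**Condensed article.** Pipeline detail is often left to a fuller document. Here, however, the article itself fixes the deletion steps and the features they delete, so the conflict is on its face.

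**Conclusion.** The conflict is real, in conditional form. Followed as written, the cleaning removes items that the protocol plans to measure, and nothing protects them.

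- **Emojis:** the loss is complete if they are counted on cleaned text. E is then constant and the mutual information is exactly 0. That they are counted on cleaned text is implied, not stated.
- **Pronouns and function words:** lost under a typical stop list, if counted on cleaned text.
- **Negations:** lost only if the list includes them. Where they are lost, emotion scores for negated sentences can be distorted in either direction, to the extent that the scoring tool would have used the negation.
- **Emotion scoring and row removal:** here the order is explicit. Scores come from filtered text, and emptied and long posts are dropped.

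The share of real posts affected cannot be estimated from the protocol. The six posts and the two tables show the mechanism, not its frequency. The point should be corrected before features are extracted.

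**What to change.** State two text streams.

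1. **Raw deidentified post:** compute linguistic-style counts, emoji features (including E) and emotion scores here, with no prior low-frequency word filter.
2. **Cleaned text:** apply the Content Analysis cleaning only to the TF-IDF features, with a named stop list that keeps negations.

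Do not drop emptied or long posts before the first stream has been extracted.

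The cost is a reordered pipeline and slightly more computing time. No additional data are needed.

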#### SM Engagement Analysis

People tend to express their emotional state to others. These days, SM has become the main platform [42] where people express themselves through writing. However, engagement on SM varies because of the mental condition of the individual. Studies have shown that people with clinical depression spend more time on SM than people without clinical depression [10,30,43]. By measuring users’ engagement, it is possible to detect their behavioral patterns [44]. To understand behavioral patterns, it is very important to observe emotions such as anger, disgust, fear, happiness, sadness, surprise, shame, and confusion [45]. The observation of the number of daily posts is a fundamental evaluation metric for this project [46], and the details of depressive lexicon analysis will be provided elsewhere. Post segmentation and word representation are 2 approaches that have been used to analyze the results of the depression detection test more effectively. In post segmentation, the sentences are split into words; in word representation, the words are converted into vectors [43]. However, the understanding of how people communicate their feelings through text has not received much attention. After analyzing the premedication and postmedication longitudinal data of a person diagnosed with MDD, it has been clearly stated that the posting pattern has significantly changed the outcome measure, indicating that SM use is affected by a person’s mood [47]. Therefore, an efficient strategy for this study is to concentrate on the text features to understand the user’s mental state and transform them into a quantifiable shape.

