### Principal Findings

Our study will begin by administering basic questions to users, followed by a filtering process to select suitable participants for our study. Upon obtaining the Facebook data, our analysis will commence. We will initially determine whether Facebook serves as the primary SM platform for the participants, a crucial factor influencing the accuracy of our predictions. In case it is their main platform, we will focus on their interactions, encompassing messages, posts, comments, and gaming activities. Our analysis will extend to anonymous actions and their engagement with content related to depression.

Conversely, in instances where Facebook is not the predominant medium, judicious focus is shifted to the advertisement analysis model. This model hinges on deciphering users’ web-based behavior, scrutinizing their browsing history, visited sites, and thematic inclinations, particularly within realms such as consultancy or support services. For participants who primarily use other platforms, our analysis will shift to evaluating the types of websites they frequent and the content they engage with. This system will work privately to assess the risks associated with anticipated changes in the future while taking into account metrics related to SM activity. We aim to demonstrate a significant correlation among Facebook games, user profile information, and content such as advertisements on mental health as depicted in Textbox 1.

Finally, we will incorporate an assessment of the frequency of their posting, commenting, friend engagement, and previous questionnaire responses, thus enhancing the depth and accuracy of our predictive model. Our ultimate prediction will amalgamate these distinct analyses through advanced techniques. Informed by the outcome of these individual models, our predictive synthesis advances, culminating in a definitive assessment of the presence or absence of suicidal ideation.

Consideration of data variables for suicidal ideation detection based on Facebook activity status.If a user is active on Facebook9-item Patient Health Questionnaire (PHQ-9) scoreFacebook games analysisBio analysisPost and comment analysis with or without the user’s nameNotification analysisKinds of groups joined and pages liked analysisSearch history analysisAdvertisement analysisDiurnal activity valueNetwork attributes calculation

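### Whole posts are deleted for being long, solely for training efficiency, so the text model is trained and tested on a length-filtered set of posts

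*Protocol article*

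**What the plan says.** All references are to the protocol article.

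- **The rule.** In the data-cleaning paragraph of Content Analysis, "the outlier rows with high word counts, deviating significantly from the majority, will be removed to optimize model training efficiency". No cut-off is given. The paragraph closes by saying that these measures prepare the data set for later analysis and for training.
- **The unit.** The next paragraph, on the vectorizer, requires that "a word must appear in at least 50 documents (posts, in our case) to be included in the feature representation". A row is therefore a whole post.
- **The representation.** The vectorizer is capped, so that "only the top 5000 most relevant features (based on their frequency) will be selected for further analysis".
- **The planned features.** In the Overview of Text and Behavior Analysis, "Post-centric behaviors include post time, number of posts, posting frequency, friends, followers, likes, replies, comments, and emoji counts". Under user-centric behavior, "Linguistic style specifically shows the total word count, first-person and third-person pronouns, functional words, assent, negation, etc". Principal Findings adds that "we will incorporate an assessment of the frequency of their posting, commenting, friend engagement, and previous questionnaire responses" in the final prediction.
- **The order of steps.** The opening of Methods lists data preparation ahead of feature engineering, training and evaluation. ML Modeling splits the data set 7:3 into training and testing sets.

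**The concern.** Long posts are not described as errors, spam or duplicates. They are valid data, removed for convenience and on the value of a quantity, word count, that the plan also wants to use as a feature.

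Two things are at stake. First, if the long posts are absent from the test set as well, then precision, recall and F1, the metrics to which the article gives most weight, are estimated on an easier or at least a different set of posts from the one participants uploaded. The Introduction presents the model as a screening and symptom-tracking tool, and users of such a tool will write long posts too. Second, if the length and count features are derived after the filter, they are distorted by it, and total word count is distorted far more than the number of posts.

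**Working it through.** **Step 1: does the rule reach the test data?** The article gives no figure for this rule, so there is nothing to reproduce, and the question is settled by setting the text side by side. Content Analysis applies the rule to the data set as a whole. The opening of Methods places preparation before training and evaluation. ML Modeling then splits the data set. No sentence confines the rule to training data or returns long posts to the test set. Read as written, the rule applies to both.

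**Step 2: does the rule reach the word-count and post-count features?** This is not settled. The order of stages in Methods points to yes. Against that, the rule acts on text that has already been preprocessed, and that preprocessing removes stop words, symbols and special characters. The pronouns, functional words and emoji counts listed as features could hardly be measured on such text, so at least some features must come from the raw upload. The protocol does not say on which side total word count, number of posts and posting frequency fall.

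**Step 3: how much could be removed?** The cut-off and the distribution of post length are not in the document. As an illustration only, assume that post length is lognormal with median 1 (the result does not depend on scale) and log-SD s. For a cut-off t, let k = ln(t)/s. Then

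- share of posts removed = 1 − Φ(k)
- share of words removed = 1 − Φ(k − s)

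Two common outlier rules are tried: t = Q3 + 1.5 × IQR, and t = mean + 3 SD.

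Worked for s = 1.0:

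- Quartile rule: Q1 = exp(−0.6745) = 0.509 and Q3 = exp(0.6745) = 1.963, so t = 1.963 + 1.5 × 1.454 = 4.143 and k = ln 4.143 = 1.422. Posts removed = 1 − Φ(1.422) = 7.8%. Words removed = 1 − Φ(0.422) = 33.7%.
- Mean + 3 SD: mean = exp(0.5) = 1.649 and SD = 1.649 × √(e − 1) = 2.161, so t = 8.132 and k = 2.096. Posts removed = 1.8%. Words removed = 1 − Φ(1.096) = 13.7%.

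| log-SD | Rule | Posts removed | Words removed |
|---|---|---|---|
| 0.8 | Q3 + 1.5 IQR | 6.2% | 23.1% |
| 0.8 | mean + 3 SD | 1.9% | 10.0% |
| 1.0 | Q3 + 1.5 IQR | 7.8% | 33.7% |
| 1.0 | mean + 3 SD | 1.8% | 13.7% |
| 1.2 | Q3 + 1.5 IQR | 9.1% | 44.7% |
| 1.2 | mean + 3 SD | 1.6% | 17.2% |

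The range is about 2% to 9% of posts and 10% to 45% of words. The first scale is the relevant one for the text model, where each post is one row, and for post counts. The second is relevant only to total word count, and only if it is computed after the filter.

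**The case against.** The strongest reply is that filtering out posts of outlying length is a discretionary preprocessing choice, and that the cut-off is a detail which a condensed article leaves to the full protocol. The second half stands: the missing cut-off is not counted here as a fault. The first half stands only in part. The rule itself is stated, it deletes valid data, and its only stated reason can be met without deleting any row.

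Several stronger readings are tempting, and the documents do not support them.

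- **That word count, post counts and the hourly shares in the diurnal formula are certainly distorted.** A reader might infer this from the order of stages. But some features in the same lists must come from raw data, and the Diurnal Activity section sets out its own cleaning steps, none of which removes long posts. Distortion of these features is possible but not shown. The sentence in SM Engagement Analysis that "The observation of the number of daily posts is a fundamental evaluation metric for this project" does not settle it: it stands under Related Work and speaks of a metric, not of which posts are counted.
- **That the filter removes the disclosures that matter most.** Nothing in the article shows that long posts carry more depressive or suicidal content. The examples under Content Analysis are short phrases, quotes, memes and songs, and Advertisement Analysis reports that participants post less when mood is low. The direction of any bias is unknown.
- **That deleting long posts saves no computing time.** The cap of 5000 terms limits the number of columns, but topic modeling, keyword extraction and emotion scoring all work on the words themselves, so long posts do cost more. Some efficiency gain is real.
- **That a participant who loses one long post is lost to the model.** The textbox in Principal Findings lists several other inputs for active users, among them the PHQ-9 score, search history, groups and pages, advertisements and network attributes.

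It is also fair to say that a deployed tool could apply the same filter. The article does not say so, and if it did, the tool would ignore those posts in use.

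**Conclusion.** The point holds in a limited form. As written, the rule takes valid long posts out of both the training and the test data of the text model, for efficiency alone, and the reported performance will describe a length-filtered set of posts. This rests on reading the opening of Methods, Content Analysis and ML Modeling together; no single sentence states it, and none contradicts it.

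Whether total word count, number of posts and posting frequency are affected is open. If they are taken after the filter, word count is cut off at the top and post counts are slightly undercounted. The illustration of about 2% to 9% of posts and 10% to 45% of words rests on an assumed lognormal distribution, an assumed log-SD of 0.8 to 1.2 and two assumed cut-offs. It shows that a small share of posts can hold a large share of the text; it is not an estimate for this study.

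**What to change.** 1. Replace the deletion of high-word-count rows by a cap: pass at most a fixed number of words of each post to the vectorizer, state that number, and keep the row.
2. State that word count, number of posts, posting frequency and timing features are computed on all uploaded posts before any text cleaning.
3. Apply the same handling to training, test and deployment data.

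The cost is one changed preprocessing step, slightly more computing time, and the loss of text beyond the cap. The second item also removes the uncertainty over which data the features come from.
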